## Interventions

### Intervention description {11a}

#### Lenio

The self-help Internet-intervention Lenio is based on principles of cognitive-behavior therapy (CBT) and its “third wave” properties (e.g., mindfulness-based and metacognitive techniques). Lenio includes a welcome module, an introduction module, and nine specific modules that all address chronic pain and emotional problems (see Table 2 for an overview of all modules). Some modules are more generic (e.g., social competence, self-worth), whereas other modules are more specific to chronic pain (e.g., modules on acceptance and commitment therapy [ACT], specific needs, and relapse prevention).

**Table 2 Tab2:** Lenio modules

Module title	Module subunits	Description
Welcome		Motivate participants to work on psychological aspects of chronic pain; goal setting
Introduction	Introduction	Participants are introduced to various features of the program
	Things to know about pain	Information about chronic pain, pain management, emotional problems, and how these are all interrelated
	What can you expect from an Internet-based program?	Expectations and prejudices regarding Internet-based self-help programs are discussed
	Exercises to get you started	Introductory exercises introduce participants to Lenio
Basic needs	Basic needs	Psychological background of humans’ basic needs. The basic psychological needs are examined and put into the context of chronic pain management
Sleep	Introduction	Importance of sleep for mental and physical well-being
	Sleep disorders	Unhealthy sleep patterns are examined and explained through illustrations and examples
	Sleep hygiene	Improvement of participants’ sleep hygiene and thus improvement of overall health
	Cognitive biases	Cognitive biases related to sleep problems, strategies to modify dysfunctional thoughts
Attentional control and mindfulness	Attentional control	Integration of mindfulness exercises into everyday life
	Introduction to mindfulness	Concepts and background of mindfulness and its importance in the treatment of chronic pain are explained
	Mindfulness exercises for everyday life	Mindfulness techniques to reduce pain and improve participants’ mental health
	Mindfulness exercises with audio instructions	Various audio exercises make it easy to work on the implementation of these exercises
Modifying thoughts	Introduction	Dysfunctional thoughts and the consequences of these thoughts on pain and emotions
	Thinking distortions	Exercises to help turn dysfunctional thoughts into more realistic and helpful thoughts
	Dealing with thinking distortions/ABC scheme	Metacognitive elements
Acceptance and Commitment	Introduction	Introduction to the theory of acceptance and commitment therapy
	Acceptance	Theory of being accepting and the importance of acceptance
	Commitment	Theory of living a value-oriented life and minimizing energy spent fighting negative thoughts and feelings
	Take action!	Interactive elements and tools to encourage self-reflection and (re)orientation of one’s personal values
Social competence	Introduction to social skills	Examination of various social skills
	Representing one's own interests	Helpful advice on how to represent one’s interests
	Forming relationships	Helpful advice on how to form relationships
	Gaining sympathy	Helpful advice on how to develop communication skills
	Overcoming blockages/resistances	Demonstration of a set of strategies for cooperative and firm communication
Self-worth	Introduction	Relevance of self-worth to general mental health is emphasized
	Self-esteem	Participants are encouraged to identify their strengths
	Unfair comparisons	The effects of low self-esteem on chronic pain are addressed
Relapse prevention	My individual warning signals	Identifying one’s warning signals of relapse
	Introduction to self-determined relapse prevention	Helpful tools and resources to deal with relapse
	Emergency plan	Interactive worksheets with important personal information (e.g., pain medications, phone number of therapist) to use in an emergency
Incorporating positive activities	Introduction	The importance of positive activities for mental health and pain symptoms
	Stopping the downward spiral	Strategies to get out of passive withdrawal behavior and support to break out of a downward spiral
	Incorporating positive activities	Strategies to incorporate positive activities
	Goals	Goal setting

Modules are further divided into subunits. For example, the module *Sleep* is further divided into *Introduction*, *Sleeping problems*, *Sleep hygiene*, and *Cognitive distortions*. Participants are free to decide on the order in which they work on the modules. Once they decide on one module, they are advised to work through all its subunits in the given order. However, the division into subunits enables users to set priorities or to skip topics if they are already familiar with them. Moreover, participants do not have to work through one module in one session, as they can pause at any time and easily return to the last page visited, which will automatically be saved. Furthermore, we recommend they work through at least two modules per week. The time required to complete one module is 30 to 60 min on average.

When participants log into Lenio for the first time, an introductory video starts automatically that contains information on how to use Lenio. Subsequently, the *welcome module* starts, which was developed based on the theory of motivational interviewing. Participants start an interactive dialogue with an avatar. The aim is to motivate participants to work on the psychological aspects of their chronic pain. At the end of the *welcome module*, participants are introduced to five different avatars whose stories will be told in case vignettes throughout the program. All other modules include psychoeducational texts as well as interactive exercises and worksheets, graphics, videos, and audios. Participants are also provided with the possibility of communicating with a moderator via an internal messenger service. If participants have technical difficulties, the moderator will answer questions related to the program within three workdays. The moderator does not provide therapeutic guidance. Thus, Lenio is an unguided Internet-based intervention.

#### COGITO

The smartphone app COGITO can be accessed and downloaded via links to the Google Play Store (for Android users) and the App Store (for iOS users) that are provided in the desktop application Lenio. In the introduction module, participants are instructed on how to use the app. By sending daily push notifications with short exercises (reading time maximum 30 s) and providing elements of gamification (e.g., collecting medals for finished exercises), COGITO demonstrates high usability. Participants will be able to choose the time and frequency of push notifications. COGITO offers different packages of exercises (e.g. *Mood and Self-Esteem, Psychosis, Gambling Problems, OCD, Chronic Pain*). Participants will be instructed to activate the packages Chronic Pain and Mood & Self-Esteem. Most packages are deactivated by default but can be individually activated by the users. As with Lenio, COGITO exercises are based on CBT and third-wave techniques.

#### MCT & More

The active control group will receive access to the smartphone app MCT & More. As MCT & More is a pilot version of the COGITO app, its design and concept are similar to COGITO. MCT & More contains three packages (Mood, Metacognitive Training, and Gambling). However, the app does not contain pain-specific exercises. Participants in the active control group will be free to choose the packages they want to receive exercises from.

### Outcomes {12}

The primary outcome will be pain impairment (mean value of impairment in daily life, free time, work) as assessed by the DSF (German pain questionnaire). The DSF is a commonly used, reliable, and validated instrument for the assessment of chronic pain [9]. We decided on pain impairment as the main outcome as Lenio especially targets the psychological aspects of chronic pain. Hence, we expect a significant improvement in different aspects of life, including daily life, leasure time, and work. The secondary outcomes will include depressive symptoms as well as the severity of pain symptoms. Furthermore, subjective evaluation and possible side effects will be assessed.

#### Primary outcomes

##### The German Pain Questionnaire (DSF)

The DSF is a reliable and valid self-report questionnaire used to assess pain symptoms [9, 41]. It captures pain in a multidimensional manner. It assesses pain location (e.g., head coded as “0” if no headache is reported and coded with “1” if it is reported), subjective description of pain, onset and course of pain, and the presence and characteristics of pain attacks. In addition, participants are asked to rate pain intensity (current intensity, mean intensity, highest intensity in the last 4 weeks, and tolerable intensity after successful treatment) on a 10-point scale (“no pain” to “strongest pain imaginable”). The number of days of illness and the pain-related impairment of everyday life (0 “no impairment” to 10 “total impairment”) are also assessed. The DSF assesses previous treatments, the number of stays in rehabilitation clinics, physician visits, surgeries, and comorbid illnesses.

Items of the DSF addressing well-being, anxiety, and depression will not be included in the survey as these dimensions are assessed by other questionnaires (e.g., BDI-II, PHQ-9). Moreover, some items will be excluded because they are irrelevant to this study. For all measurement time points, the pain intensity will be calculated according to von Korff [53].

#### Secondary outcomes

##### Beck Depression Inventory-II (BDI-II)

The BDI-II [3] is a 21-item self-report questionnaire that assesses depressive symptoms over the past two weeks. Scores range from 0 to 63, with higher scores indicating higher levels of depression (0–8 = no depression, 9–13 = minimal depression, 14–19 = mild depression, 20–28 = moderate depression, and 29–63 = severe depression). Internal consistency is good, with Cronbach’s α of 0.89 [17]. In a sample of pain patients, comparable results were found [7, 43]. For all measuring points the BDI will be assessed. For our analysis, the sum score will be calculated.

##### Patient Health Questionnaire-9 depression module (PHQ-9)

The PHQ-9 [2, 29] is a self-report questionnaire measuring depressive symptom severity over the previous week. The PHQ-9 has high internal consistency (Cronbach’s α = 0.86–0.89, [29]. Its scores range from 0 to 27, with scores from 0 to 4 indicating minimal depression, 5–9 mild depression, 10–14 moderate depression, and 15–27 severe depression. For all measuring points, the sum score will be calculated.

##### Web Screening Questionnaire (WSQ)

The WSQ is a brief online self-report instrument that screens for common mental disorders such as affective disorders, alcohol abuse/dependence, general anxiety disorder, posttraumatic stress disorder, social phobia, panic disorder, agoraphobia, specific phobia, obsessive–compulsive disorder, and suicide risk. Sensitivity ranges between 0.72 and 1.00, and specificity ranges between 0.44 and 0.77 [14]. The WSQ will be assessed at baseline and for the analysis, the sum score as well as the cumulative values for all subscales of the WSQ will be calculated.

##### Injustice Experience Questionnaire (IEQ).

The IEQ is a valid and reliable tool for the assessment of perceived injustice in people suffering chronic pain, with a Cronbach’s α of 0.92 [50]. The IEQ consists of 12 items that assess thoughts of unfairness related to symptoms on a 5-point scale ranging from “never” to “all the time.” Perceived injustice is examined by the following elements: severity of loss consequent to injury, blame, sense of unfairness, and irreparability of loss. A score of 30 is the cutoff for a clinically relevant level of perceived injustice*.* For all three measuring points, the IEQ subscale “blame/injustice” and “severity/irreparability” as well as the sum score will be calculated.

##### Pain Catastrophizing Scale (PCS)

The PCS is a valid and reliable measure of catastrophizing. It assesses the thoughts and feelings of chronic pain patients. The questionnaire contains 13 items. Participants are asked which thoughts and feelings they experience during pain on a 5-point scale from “not at all” to “all the time.” Besides the total score, three subscales (rumination, magnification, and helplessness) are assessed. The PCS has demonstrated good internal consistency in the past with a Cronbach’s α of 0.87 [45]. For all three measuring points, the PCS total score as well as the subscores “helplessness,” “reinforcement,” and “worrying” will be calculated.

##### Fear-Avoidance Beliefs Questionnaire (FABQ)

The emergence of the biopsychosocial model of low back pain (LBP) led Waddell et al. [56] to develop the Fear-Avoidance Beliefs Questionnaire (FABQ, [56]). The FABQ assesses the patient’s fear-avoidance beliefs about physical activity and its contribution to lower back pain. It consists of 16 items that can be rated on a 7-point Likert scale (0 = “completely disagree” to 6 = “completely agree”). Test–retest reliability of the FABQ is excellent (ICC = 0.97, [27]). For the current study, we have adapted the FABQ to assess general chronic pain (not specifically lower back pain). For all three measuring points, the sum scores for “bodily activity” and “work load” will be calculated.

##### Pain Self-Efficacy Questionnaire (FESS)

To assess self-efficacy in our sample, we will use the German version of the Pain Self-Efficacy Questionnaire (FESS). According to Mangels and colleagues [34], the questionnaire is a valid instrument to measure therapeutic success in pain research. Specifically, it measures one’s conviction in one’s own ability to tackle activities despite suffering from pain. Additionally, it has high internal consistency, with a Cronbach’s α of 0.93. For all three measuring points, the sum scores of the PSE subscales “active coping” and “catastrophizing” will be assessed.

##### World Health Organization: Quality of Life abbreviated version (WHOQOL-BREF

The WHOQOL is a cross-cultural questionnaire assessing generic quality of life (QoL). QoL is defined as an individual’s perceptions of their position in life. QoL considers the context of culture and value systems, including personal goals, standards, expectations, and concerns. The questionnaire was developed by the WHOQOL Group of the World Health Organization. For the present study, we will use the global QoL item (“How would you assess your quality of life?”), with responses ranging from “very poor” (1) to “very good” (5). Despite its brevity, the internal consistency of the questionnaire was high (α = 0.90) in a sample of students [23]. For all measuring points, the global item will be assessed.

##### University of Rhode Island Change Assessment Scale (URICA)

The URICA is a self-report questionnaire developed to assess various stages of change in complex problem behavior [35].The URICA has demonstrated high internal consistency, with a Cronbach’s α of 0.77 to 0.82 and good reliability [15]. It predicts both treatment success as well as drop-out rates [35]. The present study will use the German version of the URICA (Fragebogen zur Erfassung der Veränderungsbereitschaf, FEVER, [19]). The FEVER captures three different phases of change: (1) pre-contemplation, i.e., lack of readiness to engage in an intervention or no readiness to change, (2) contemplation, i.e., readiness to engage in an intervention or to change something, and (3) action, i.e., the decision to change something and the use of active strategies to change. For the current study, a shorter version with only three items per phase (total of nine items) will be used. The FEVER/URICA will be assessed at baseline only. The subscales “precontemplation,” “contemplation,” “preparation,” “action,” and maintenance” will be calculated.

##### Credibility/Expectancy Questionnaire (CEQ)

For reasons of test economy, only one item of the CEQ [4, 12] will be used. The CEQ measures treatment expectancy (“What do you think at the present time about how successful the self-help program Lenio offered here will be in alleviating your complaints?”), which can be rated on a scale from 1 (“not successful at all”) to 9 (“very successful”). The CEQ item will be assessed at baseline only.

##### PANEPS

The Positive and Negative Effects of Psychotherapy Scale (PANEPS) is a self-report questionnaire that assesses positive effects and adverse events during the most recent session of psychotherapy [42]. The PANEPS consists of 29 items on four subscales: Positive Effects, Unethical Conduct, Malpractice, and Side Effects. Internal consistency is high for all subscales, with a Cronbach’s α of 0.72 to 0.92 [40]. In the current study, an adapted version (PANEPS-I) will be used that has not been validated yet (e.g., the wording of some items has been adapted). All four sub scores will be calculated for post and follow-up assessment.

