### Ethical aspects and data safety

The study will be conducted in accordance with the Guidelines for Assuring Good Scientific Practice and the Principles and Responsibilities for the Conduct of Clinical Trials of the German Research Foundation (DFG). An ethics vote in support of the project has been obtained from the Local Psychological Ethics Committee of the Center of Psychosocial Medicine at the University Medical Center Hamburg-Eppendorf (LPEK-0078a). The study will be conducted in accordance with the Declaration of Helsinki. Any adverse events will be documented and reported {22}. Participants must sign informed consent prior to study participation, which informs them about the study procedure, data protection risks and compensation, and their right to withdraw from participation at any time without giving a reason. If they withdraw, all their data will be deleted.

The research project will be carried out in accordance with the EU General Data Protection Regulation. All other data will be stored on password-protected computers. Data collection will be conducted online using the survey software Qualtrics®, which guarantees high data protection standards such as end-to-end encryption. After completion of the study, the collected data will be archived for 10 years (e-mail addresses will be deleted after the end of the study). The clinical principal investigator (PI) will be responsible to carry out the study in accordance with the study protocol {5d}. The PI will ensure that everyone working in the research project is sufficiently qualified.

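### The only named harm scale, PANEPS-I, cannot support a controlled comparison of harm with the waitlist; worsening rates from scores already collected can

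*Protocol article*

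**What the plan says.** The *Outcomes {12}* section of the protocol article lists possible side effects among the things to be assessed. *Participant timeline {13}* places this at post-intervention and follow-up and does not limit it to particular arms.

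The only instrument named for the purpose is in *Secondary outcomes – PANEPS*. The parent scale "is a self-report questionnaire that assesses positive effects and adverse events during the most recent session of psychotherapy". On its structure: "The PANEPS consists of 29 items on four subscales: Positive Effects, Unethical Conduct, Malpractice, and Side Effects". For this trial, "an adapted version (PANEPS-I) will be used that has not been validated yet (e.g., the wording of some items has been adapted". The scoring rule follows: "All four sub scores will be calculated for post and follow-up assessment".

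On the intervention, the *Lenio* section states: "The moderator does not provide therapeutic guidance. Thus, Lenio is an unguided Internet-based intervention". *Trial design {8}* presents the waitlist as the no-treatment comparator. *Study setting {9}* and *Participant timeline {13}* give both control arms access to Lenio only after the 16-week survey; until then the active control has the MCT & More app and the waitlist has nothing.

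*Statistical methods {20a}* analyses primary and secondary measures by ANCOVA, with baseline scores as covariates, allocation as the factor, and post and follow-up scores as dependent variables. *Ethical aspects and data safety* adds: "Any adverse events will be documented and reported {22" (the number is the SPIRIT item).

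**The concern.** A harm outcome in a three-arm trial is most useful when every arm can answer it in the same way. Here the named scale comes from face-to-face psychotherapy and two of its four subscales concern a therapist's conduct, while the programme has no therapist. One randomised arm has had no programme at either time when the scale is scored.

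Low conduct scores would then be expected whatever the programme does, and a side-effect score would have no waitlist counterpart. Either could be quoted as evidence that Lenio is safe when it mainly reflects the instrument. The ANCOVA of mean symptom scores does not fill the gap, because a mean improvement can coexist with a subgroup that worsens.

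**Working it through.** The plan gives no figure for harm, so the first two steps set its statements side by side. The third gives the precision of the proposed replacement.

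**1. Does PANEPS-I have a referent in each arm before week 16?** The item wording of PANEPS-I is not shown, so take the three ways in which it could have been adapted, with 100 participants per arm (*Sample size {14}*):

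| Frame of the adapted items | Lenio | MCT & More | Waitlist | Without a referent in the trial |
|---|---|---|---|---|
| Psychotherapy session kept | none | none | none | 300 of 300 |
| Reworded to Lenio (as the article does for the CSQ-8) | yes | none | none | 200 of 300 |
| Reworded to any programme used | yes | yes | none | 100 of 300 |

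Under every reading, treatment-referenced items have no referent in the waitlist arm. Under the most favourable one, that is one arm in three. The Unethical Conduct and Malpractice subscales, 2 of 4, have no evident therapist to refer to in any arm. The internal consistency quoted in the section (0.72 to 0.92) precedes the statement that the adapted version is not validated, and so cannot be taken as a property of PANEPS-I.

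**2. Does the scale fit the stated analysis?** PANEPS is listed under secondary outcomes. The ANCOVA needs a baseline score; PANEPS-I is scored at post and follow-up only. The model as described cannot be fitted to it. The descriptive route in *Methods for additional analyses {20b}* is written for subjective evaluation and does not mention side effects.

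**3. What could a worsening rate show?** BDI-II is assessed at all measuring points. DSF pain impairment is the primary outcome and is needed at baseline, post and follow-up for the ANCOVA.

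Inputs: n observed per arm = 100 × (1 − 0.25) = 75, from the planned 25% drop-out. The worsening rate p is not in the document; 10% is an assumption, shown here with 5% and 20%.

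- Per arm: half-width = 1.96 × √(p(1 − p)/75)
- Difference between two arms with the same p: half-width = 1.96 × √(2p(1 − p)/75)

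| Assumed p | Per arm | Difference |
|---|---|---|
| 5% | 1.96 × √(0.0475/75) = 4.9 points | 1.96 × √(0.095/75) = 7.0 points |
| 10% | 1.96 × √(0.09/75) = 6.8 points | 1.96 × √(0.18/75) = 9.6 points |
| 20% | 1.96 × √(0.16/75) = 9.1 points | 1.96 × √(0.32/75) = 12.8 points |

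These half-widths describe the proposed outcome. They do not measure a bias in the present plan.

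**The case against.** The strongest reply is that much of the criticism could rest on text that is not shown. The session frame belongs to the parent scale. PANEPS-I may have been reworded sensibly, as the CSQ-8 was, and the article says openly that it is not validated. The assessment schedule (Table 1) is not reproduced, so who completes the scale is unknown. All of this stands. Nothing should be asserted about the recall period of PANEPS-I, or that only Lenio users complete it.

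A reader might infer that harm is measured by this scale alone and cannot be compared between arms. The article does not support that. It provides separately for documenting and reporting adverse events, and how these are elicited may properly sit in the full protocol. BDI-II, PHQ-9 and DSF scores are collected in every arm, so average worsening against either control would show in the planned ANCOVA.

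The missing baseline is also a limited point. Randomisation would permit an unadjusted comparison of post scores between the two programme arms. It rules out the stated model, not every comparison.

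A reader might also infer, from "The WSQ will be assessed at baseline", that the suicidality item should be repeated later. That is not part of this point: recruitment is complete, and a repeated item would need a safety-response procedure that cannot be settled in an analysis plan.

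What survives does not depend on unseen wording. Under every plausible adaptation the waitlist has no programme to rate, and the plan commits to therapist-conduct scores for a programme without a therapist.

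**Conclusion.** The point holds in a limited form. PANEPS-I, the only named harm scale, cannot support a controlled comparison of harm with the waitlist, and its therapist-conduct scores carry no information about the safety of an unguided programme. At least 100 of 300 participants and 2 of 4 subscales are affected.

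This rests on two assumptions: that the PANEPS-I items refer to a treatment or programme, and that the two conduct subscales mean what their names say. It does not show that harm goes unrecorded, and it does not touch the primary outcome or the sample size. It is worth correcting because the data for a controlled harm statement are already being collected and the article defines no outcome that uses them in this way. The precision of such a statement would be modest: large differences in worsening could be excluded, small ones could not.

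**What to change.** 1. Before the outcome analysis, define a harm outcome that is identical in all three arms: the proportion with reliable worsening from baseline to week 8 and from baseline to week 16, on DSF pain impairment and on BDI-II. Fix the reliable-change threshold for each scale in advance and state the reliability and standard deviation used. For BDI-II, the article's α of 0.89 would give 1.96 × √2 × √(1 − 0.89) = 0.92 baseline standard deviations. The article gives no reliability for DSF pain impairment, so its source must be named.
2. Report the proportions per arm, and the differences between Lenio and each control, with 95% confidence intervals.
3. Report PANEPS-I descriptively, only in arms that used a programme, and state its recall period. Do not present the Unethical Conduct and Malpractice scores as evidence of safety.

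The cost is a paragraph in the analysis plan and one results table. No new data, survey items or participants are needed.
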